### Baseline assessment

Participants who meet the eligibility criteria will complete two weeks of daily logs to monitor baseline food intake and timing via a cellphone app. Enrollment in the intervention will be contingent on the adequacy of their dietary logging on the app during the baseline period. Participants will be considered to have adequate logging for a given day if they enter at least two logs at least five hours apart (they will receive information about how to add missed entries). Participants who report a much shorter time window than they did on the screening questionnaire will be reminded to capture each eating epoch, and queried if the interval logged is substantively shorter. Participants’ logging will be reviewed on the first and second days after baseline, and participants will be given the opportunity to troubleshoot with staff as needed. Thereafter, the logs will be monitored at least twice per week. Those who successfully complete logs will receive encouraging messages through the logging app. At the end of the first week, participants with no days of adequate logging will be excluded from the study (unless we identify a barrier that can be addressed). After 10 days, those who have completed less than 50% of their assigned logs will be reminded that study continuation will depend on successful logging and given an opportunity to receive support around barriers to logging; if warranted (e.g., the patient experienced technical or travel barriers), we will extend the baseline period for four additional days.

Participants who complete at least seven days of adequate dietary logs during baseline will be randomly assigned to an intervention. To allow for shopping and preparation, individuals will receive their intervention assignment 4 days before the start of the intervention, with instructions not to begin the diet until the intervention period begins.

Starting on day 5 after baseline, we will gather several daily measures sent by REDCap through text message. Participants will complete the Core Consensus Sleep Diary (Core CSD; [87]) to assess sleep quantity, timing and quality each morning for 10 days until the end of the baseline period. Participants will also complete EMA of 5 prompts per day for 8 days with brief probes to assess mood (detailed below). We will send the CSD and EMA probes on at least 2 free days for each individual (e.g., one Saturday and Sunday). After the 8 days of mood monitoring, participants will be asked to complete day-after food frequency diaries on the final two days of baseline (one free day and one workday) to capture the quantity consumed for each component of the Mediterranean Diet (e.g., fruit, vegetables, whole grains, olive oil).

After at least 3 days of adequate logging, participants will be sent links to schedule the baseline interview (longitudinal interval follow-up evaluation [LIFE]; [76, 88, 89]; Montgomery-Asberg Depression Rating Scale [MADRS]; [90]); Young Mania Rating Scale [YMRS]; [91]; and the short form of the Rey Auditory Verbal Learning Test [RAVLT]; [92, 93]) and will be asked to complete a preintervention baseline battery of online questionnaires for demographic information, symptoms, sleep, and functional information (Patient Mania Questionnaire [PMQ-9]; [94]), Patient Health Questionnaire [PHQ-9]; [95], and Brief Quality of Life in Bipolar Disorder (QoL.BD; [96]), PROMIS Sleep Disturbance and Sleep-Related Impairment [97], Sleep Household Environment and In-Bed Behaviors [98] World Health Organization Disability Assessment Schedule (WHODAS 2.0-Brief; [99]). The participants were also asked to complete measures of potential moderators (Household Food Security Survey [HFSSM]; [100]), Positive Urgency [101], Personality Traits (PID5BF + ; [102]), Risky Families [103], and for women in appropriate age ranges, the Menopause-Specific QoL Sleep [hot-flash] items [104, 105]).

### Assessments during the intervention and follow-up

Participants will be asked to complete daily food logs using brief text entries and optional photos with a cellphone app throughout the 8-week intervention period. At 6, 9, and 15 months after the end of baseline, participants will log their food (first intake and last intake) for 10 days in the app. Sleep diaries (core CSD) and EMA data will be collected for 8 days at the midpoint of the intervention. For one weekday and one weekend after the EMA ends, all participants will be asked to provide day-after food frequency diaries to be able to code Mediterranean diet adherence. Symptom severity and LIFE interview assessments will be conducted at the midpoint, at the end of the intervention, and at 6, 9, and 15 months after the end of baseline. Self-rated assessments of symptom severity, QoL, and sleep/circadian variables will be conducted at each of those assessments and at 16 weeks post baseline. The secondary outcome and eating disorder measures will be administered postintervention but not at follow-ups.

### Assessment of training and reliability

Before commencing the study, interviewers will be trained to standardize the administration and to attain high interrater reliability on all observer-rated measures (the DIAMOND, SCISD-R, C-SSRS, LIFE, MADRS and YMRS). Interrater reliability reviews will be conducted monthly on randomly selected recordings throughout the trial. If rater drift is identified, assessors will be retrained.

## Strategies to maximize data quality

As noted above, we will exclude participants who provided careless responses during the screening questionnaire. In self-rated assessments during the intervention and follow-up, we will exclude data from any bundle in which participants fail 50% or more of the attention checks [1] or when the mean duration for completion of standard multiple-choice questions is < 2 s. At the midpoint, at the end of the intervention, and at the follow-up assessments, we will ask participants whether we should exclude their data from that session due to problems with attention or understanding. Comprehensive data cleaning (range and other distributional checks, comparison with published norms where relevant) will be conducted before the analyses.

## Risk management

Risk management procedures are based on recent online self-help interventions in BD and on websites for BD [106, 107]. In this population, evidence that a participant is experiencing active suicidality would be of particular concern. All staff members will be trained to alert a licensed clinical psychologist if they learn of active suicidality (ideation coupled with intent, plan, preparation or a history of suicide attempt). As part of enrollment, we will clarify that participants will be required to continue to work with their local treatment team for their care, as we are not able to provide emergency services and do not review patient information in real time. We will require a release of information to contact a treatment provider in case of concerns about suicidality, and we will provide the participant with a letter for their provider that outlines their patient’s involvement in our study. This letter will clarify that primary treatment for the participant remains with their provider and that we may contact their provider if we are concerned about the participant’s wellbeing. At each assessment of pharmacotherapy, we will check to see if there has been a change in the provider; if so, we will gather a new release information. If we become aware of acute risk of suicidality, we will work collaboratively with patients to enhance their contact with the provider. We will inform all participants that if we are concerned about suicide risk, we may be mandated to contact their provider or authorities to intervene. We will provide resource information as part of consent (unsuicide.org, 988).

To monitor the potential development of eating disorder symptoms, we will administer the EDE-QS at the end of week 2 of the intervention, as well as at mid- and postintervention. Scores above the clinical threshold will be assessed using procedures detailed below.

### Adverse events

In addition to the risk management procedures outlined above, we will take several steps to minimize the potential for adverse events. All team members involved in clinical assessments, coaching, or otherwise in direct contact with participants will receive careful training concerning self-harm, suicidality, and elevated eating disorder, mania or depression symptom severity scores. A detailed manual will provide assessment probes, decision rules, referral resources, and contact information for use during emergency situations. Training will emphasize procedures for providing feedback in a clinically sensitive manner, and role plays will be conducted to cover legal and ethical guidelines, including situations in which we do and do not have the authority to share concerns with treatment providers and/or emergency departments. Team members will be trained about the specific situations in which we have permission to break confidentiality and contact their treatment provider or emergency services, as well as be trained in the C-SSRS Interview to assess current intent, plan, and means and history of attempts. Interviewers will be trained to contact a licensed clinical psychologist while on the phone/videoconference if any participant endorses significant suicidal ideation, and clear flow charts will be available that detail “significant suicidal ideation” (e.g., intent, plan, or means are endorsed; history of suicide attempt with current suicidal ideation).

Feedback and referrals for participants will be provided based on the judgment of urgency of the situation. In situations that do not necessitate emergency intervention, the researcher reviews the nature of the symptoms with the participant and provides support for sharing these concerns with their provider. We will encourage sharing information with providers if participants are experiencing symptoms that meet the diagnostic criteria of the DIAMOND or the LIFE for a hypomanic, manic, or depressive episode or if the MADRS score ≥ 19 [108]. More intensive interventions might involve collaborating to remove lethal means or conjointly contacting treatment providers with the participant to facilitate effective communication. As warranted, the researcher will follow-up with the participants to ensure that they were able to receive adequate support. At all times, we balance respect for autonomy with the need for safety. Participants who experience symptoms that would interfere with the demands of the protocol will be granted a break from following the food plan and logging, and interviewers will schedule a time to check in to consider restarting trial engagement.

Throughout the trial, participants will be encouraged to reach the PI with any concerns about the study. Adverse events will be assessed formally post-intervention and at each follow-up. We may also learn of problems as participants complete logs (e.g., food restriction) or interact with coaches.

All sources of information will be monitored in a timely manner to consider potential adverse events. Where clinical deterioration is noted as potentially emerging, researchers will attempt to assess whether emergent symptoms or concerns appear in any way connected to the intervention or study procedures. If EDE-QS symptoms are above the clinical threshold after enrollment, we will include a probe to assess intervention effects on those symptoms (e.g., do you believe that this intervention has triggered food or appearance symptoms for you?), and we will conduct clinical interviews to consider deterioration of symptoms. Participants will be withdrawn from the trial if their participation compromises clinical care as determined by the study’s executive committee. On a case-by-case basis, this might include instances of hospital admission, acute hypomania or mania, psychotic symptoms, active suicidal intent, or increased eating disorder symptoms, particularly where there is concern that deterioration is related to trial engagement.

Adverse events will be reviewed at monthly executive meetings and at least annual meetings of the independent trial committee (who will consider patterns of adverse events by condition). Adverse events will be promptly reported to the Committee for the Protection of Human Subjects within one week.

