## Trial design

The trial is a prospective, rater-blind, superiority randomized controlled trial (RCT) with a one-to-one allocation ratio comparing TRE with the Mediterranean diet. Participants in both conditions will be asked to sustain ongoing medical care for BD.

The primary endpoint is immediately postintervention (at completion of the 8-week intervention). The follow-up times are 6, 9, and 15 months after the baseline, with an additional 16 weeks post-baseline self-reported assessment. The study setting is remote (online).

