## Randomization

Participants will be allocated to intervention arms using a one-to-one ratio by predetermined computer-generated codes so that randomization is free of potential allocation bias. Maximally tolerated imbalance (MTI) large stick randomization will be used to match the two groups on two variables: bipolar I vs. bipolar II diagnosis and the number of hypomanic/manic episodes (coded as 1, 2, 3 +). The MTI will be set to 3. Randomization will be performed within REDCap, by a staff member not involved in assessing participants.

To reduce expectancy effects, the trial is framed as a comparison between two healthy eating interventions, and participants will not be informed of the study’s primary hypotheses. User permissions will be strictly limited, so that assessors will remain unaware of the participants’ intervention conditions. Those who become aware of the intervention condition will, if possible, be replaced. Success in masking intervention conditions will be quantified by evaluating whether interviewers are more accurate than chance when asked to guess allocation upon completion of the RCT.

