## Reasons for discontinuation from study

Participants requesting to withdraw from the study will be asked to complete an intervention acceptability survey and final assessment of symptoms (self-rated mania, depression, and QoL; and, if willing, the YMRS, MADRS, and the LIFE. They will be asked (via a brief phone call from a trial coordinator) the main reasons for discontinuation. Should adverse events be discovered, those will be reported.

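### The staff who arrange restart check-ins after a symptom-related break carry the same title as the masked outcome raters, so the check-in may expose raters to allocation

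*Protocol article*

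**What the plan says.** Under Trial design the protocol states: "The trial is a prospective, rater-blind, superiority randomized controlled trial (RCT"). Under Randomization it protects the blind in three ways:

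- Access: "User permissions will be strictly limited, so that assessors will remain unaware" of the assigned arm.
- Replacement: "Those who become aware of the intervention condition will, if possible, be replaced".
- A masking check: interviewers guess the allocation once the trial is complete, and their accuracy is compared with chance.

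The section on training and reliability has interviewers trained on all observer-rated measures, including MADRS, YMRS and LIFE. The Mood assessments section names those three as the primary outcome measures.

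The Adverse events section then deals with a subgroup: "Participants who experience symptoms that would interfere with the demands of the protocol". For this subgroup the provision is that they "will be granted a break from following the food plan and logging". As to what follows the break, the section says that "interviewers will schedule a time to check in to consider restarting trial engagement". The text does not say who grants the break, who conducts the check-in, or what it covers.

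Other roles exist. Coaches deal with the food plan in both arms (Intervention content). People who ask to withdraw are asked for their reasons "via a brief phone call from a trial coordinator" (Reasons for discontinuation from study).

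**The concern.** One job title covers the masked raters and the staff who arrange the contact about resuming the diet. Participants know their diet. Someone explaining why it was hard to follow, or whether it can be taken up again, may easily mention an eating window or particular food servings. Either would identify the arm.

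What is at stake is the masking of the primary outcomes. The exposed participants are not a random subset: they are those with symptoms that interfere with the protocol, in whom mood ratings may well be moving. If breaks, or raters' expectations about the two diets, differ between arms, any shift in ratings would also differ between arms and would enter the treatment comparison. Different break rates are conceivable, since only the time-restricted arm has a daily fasting period, but the protocol gives no data on this.

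**Working it through.** The protocol has no figure of its own on this point. The check is a comparison of sections, followed by an illustration with assumed inputs.

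**1. Are the interviewers the masked raters?** Yes, on the protocol's wording. The Randomization section speaks of assessors when it describes access and of interviewers when it describes the masking check, so interviewers are the staff meant to be masked. The training section has interviewers administer MADRS, YMRS and LIFE. No section distinguishes a second group of interviewers for the Adverse events task.

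**2. Do the safeguards cover this contact?**

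| Safeguard | What it covers | What it leaves open |
|---|---|---|
| Restricted user permissions | What the rater can see in the system | What a participant says |
| Replacement of unmasked staff | Later ratings, where possible | The exposure itself, and cases where replacement is not possible |
| Allocation guess | Measures masking overall | Comes at the end of the trial, too late to act on |

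None of them prevents disclosure in a restart contact.

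**3. How large could the effect be?** Inputs:

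- n = 100 per arm. The Statistical analysis plan section aims for 200 after 33% attrition (300 × 0.67 = 201), with one-to-one allocation.
- q = share of participants rated unmasked, 5% to 20%. Assumed; the protocol gives no break frequency.
- b = differential shift in ratings between arms among those participants, 0.25 to 0.5 SD. Assumed.

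Formulas:

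- Bias in SD units = q × b.
- Standard error of the difference in means = √(2/100) = 0.1414 SD.
- m = bias / 0.1414.
- Two-sided type I error = 1 − Φ(1.96 − m) + Φ(−1.96 − m).

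| q | b (SD) | Bias (SD) | m | Type I error |
|---|---|---|---|---|
| 5% | 0.25 | 0.0125 | 0.088 | 5.1% |
| 5% | 0.50 | 0.025 | 0.177 | 5.4% |
| 10% | 0.25 | 0.025 | 0.177 | 5.4% |
| 10% | 0.50 | 0.050 | 0.354 | 6.4% |
| 20% | 0.25 | 0.050 | 0.354 | 6.4% |
| 20% | 0.50 | 0.100 | 0.707 | 10.9% |

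At 5% unmasked the effect is negligible. It becomes noticeable only when both inputs are near the top of the range. The calculation is a simple two-mean comparison, not the planned mixed model, so it shows order of magnitude only.

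**The case against.** The strongest reply is that the text shows a possible exposure and no more. Interviewers are said to schedule a check-in. The protocol does not say that they conduct it, that they discuss the content of the plan, or that they are told the arm. Food plan and logging are neutral terms, since both arms follow a plan and log intake, and whether someone feels able to resume can be asked without naming the diet. All of this stands. A reader might infer that raters manage both the pause and the restart, and that the blind therefore breaks. The documents do not support that: the break is granted by an unnamed role, and disclosure is a risk, not a certainty. Nor do they rank these participants as the most severely ill.

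A reader might also point to the probe used when eating-disorder scores rise after enrollment ("do you believe that this intervention has triggered food or appearance symptoms for you") as a second breach. That section does not say who administers the probe or the clinical interviews that follow, and its wording does not identify an arm. A detailed manual is mentioned but not shown, so nothing can be concluded from the silence.

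The replacement clause already provides part of the remedy, and the allocation guess would help reveal a substantial failure of masking. Both points are fair, but replacement acts only after exposure and is conditional.

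Finally, the inputs to the illustration are assumed. Entry criteria exclude current mood episodes and several other acute conditions, so a 20% break rate is far from obvious, and only contacts before the week-8 interview can affect the primary endpoint. Larger error rates can be produced by assuming that ratings shift in opposite directions in both arms, but nothing in the protocol supports that scenario.

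**Conclusion.** The point holds as an inconsistency in role assignment that creates an avoidable risk to the blind. The Adverse events section gives a task concerning resumption of the diet to staff with the title of the masked raters, and the safeguards under Randomization do not close that route. It does not hold as a demonstration that the blind fails.

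The size of any bias cannot be determined from the protocol. On the assumed inputs it runs from about 0.01 to 0.10 SD, with type I error between about 5.1% and 10.9%. It could be nil if breaks are rare or the contacts stay neutral. The case for a change rests on how little it costs to protect interviewer-rated primary outcomes, not on a proven distortion.

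**What to change.** Reconcile the Adverse events section with the Randomization section:

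- State that the restart check-in is arranged and conducted by existing staff who do not rate that participant, for example the coach or the trial coordinator.
- If an interviewer nevertheless learns the arm, record it at the time and have another existing rater carry out that participant's next MADRS, YMRS and LIFE.

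The cost is slightly more scheduling and some loss of continuity for the participant. No new role, visit or measure is needed. The change concerns staffing and masking only and takes no position on when a break or a restart is clinically right.

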**Methods:**

This study is an international RCT to compare the effectiveness of TRE and the Mediterranean diet. Three hundred participants will be recruited primarily via social media. Main inclusion criteria are: receiving treatment for a diagnosis of BD I or II (confirmed via DIAMOND structured diagnostic interview), endorsement of sleep or circadian problems, self-reported eating window of ≥ 12 h, and no current mood episode, acute suicidality, eating disorder, psychosis, alcohol or substance use disorder, or other health conditions that would interfere with or limit the safety of following the dietary guidance. Participants will be asked to complete baseline daily food logging for two weeks and then will be randomly allocated to follow TRE or the Mediterranean diet for 8 weeks, during which time, they will continue to complete daily food logging. Intervention content will be delivered via an app. Symptom severity interviews will be conducted at baseline; mid-intervention (4 weeks after the intervention begins); end of intervention; and at 6, 9, and 15 months post-baseline by phone or videoconference. Self-rated symptom severity and quality of life data will be gathered at those timepoints, as well as at 16 weeks post baseline. To provide a more refined index of whether TRE successfully decreases emotional lability and improves sleep, participants will be asked to complete a sleep diary (core CSD) each morning and complete six mood assessments per day for eight days at baseline and again at mid-intervention.

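### Formal adverse-event assessment first occurs at the end of the 8-week intervention, with none stated at the existing week-4 contact or at withdrawal, so events in early leavers may be under-counted

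*Protocol article*

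**What the plan says.** The section Adverse events sets the schedule: "Adverse events will be assessed formally post-intervention and at each follow-up". Post-intervention is the end of the 8-week programme.

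There is an earlier contact with all participants. The abstract lists symptom interviews at "mid-intervention (4 weeks after the intervention begins", and the section Assessments during the intervention and follow-up confirms it: "Symptom severity and LIFE interview assessments will be conducted at the midpoint, at the end of the intervention". Self-rated measures are collected at the same time. Neither that section nor Table 2 places an adverse-event measure there.

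Other provisions apply before week 8:

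- Risk management: "we will administer the EDE-QS at the end of week 2 of the intervention, as well as at mid- and postintervention". Scores above threshold lead to a probe about the intervention's role and a clinical interview.
- Table 2: MADRS, YMRS, LIFE, PHQ-9, PMQ-9 and the global impression scales at mid-intervention, with no distinction by arm.
- Adverse events: participants are encouraged to raise concerns with the study lead. In addition, "We may also learn of problems as participants complete logs (e.g., food restriction) or interact with coaches" and "All sources of information will be monitored in a timely manner to consider potential adverse events".

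On oversight, the same section says "Adverse events will be reviewed at monthly executive meetings", and an independent committee looks at patterns by condition at least once a year.

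For people who ask to leave, Reasons for discontinuation from study requests the acceptability survey, a final symptom assessment and a short call about reasons. On harms it says only "Should adverse events be discovered, those will be reported". Statistical analysis of the primary outcome then makes an exception to the effort to obtain final assessments: it leaves out people who explicitly discontinued and people withdrawn on ethical grounds.

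**The concern.** A comparison of harms between arms needs the same question put to everyone, in the same way, at times that most participants reach. Here the first such question comes at week 8, and two existing opportunities before it go unused: the week-4 contact and the withdrawal contact.

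Two features could make the resulting gap informative. First, the article says withdrawal from the trial may follow events such as hospital admission, mania, psychosis, suicidal intent or worsening eating-disorder symptoms, so leaving early can be linked to harm. Second, opportunistic detection may not be equal. Twice-weekly log review with feedback, including on over-restriction, is written in the section Time-Restricted eating. The section Mediterranean diet asks for logging but has no matching sentence.

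What is at stake is the completeness and balance of the harms comparison, not the primary efficacy test.

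**Working it through.** **1. What is asked, of whom, and when (both arms unless noted)**

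| Time | Eating-disorder symptoms | Mood symptoms | Other adverse events |
|---|---|---|---|
| Week 2 | EDE-QS | none scheduled | spontaneous report, logs, coaching |
| Week 4 | EDE-QS | interviews and self-report | spontaneous report, logs, coaching |
| Week 8 | EDE-QS | interviews and self-report | formal assessment |
| Withdrawal before week 8 | not stated | requested | open-ended survey items and call about reasons; no formal query stated |

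The gap lies in the last column, in the rows before week 8 and at withdrawal. People who reach week 8 can report earlier events then, by recall over up to 8 weeks. The article does not state the recall period.

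**2. Whether early leavers are reached**

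The discontinuation section asks people who withdraw for a final assessment. The primary-analysis section exempts explicit discontinuers and those withdrawn on ethical grounds from the attempt to obtain one. The two sections do not say the same thing about the same people. Neither names an adverse-event form.

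**3. Whether opportunistic detection is equal by arm**

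- Intervention content says coaching is parallel in format, timing and intensity, but does not mention log review.
- Measures says logs are reviewed for completion and careless entry, which is not a check for harms.
- Twice-weekly review with feedback during the intervention appears only under Time-Restricted eating.

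A difference by arm is therefore possible on the text, but not shown.

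**4. Scale**

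Inputs: 300 recruited (abstract); 33% attrition, leaving 200 (Statistical analysis plan).

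The plan's own figure reproduces: 200 / (1 − 0.33) = 298.5, rounded up to 299, against 300 stated. In the other direction, 300 × (1 − 0.33) = 201.

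Expected attrition: 300 × 0.33 = 99. The article does not say when it occurs. Let *s* be the share that falls before the post-intervention visit (assumed). The number missing that visit's adverse-event assessment is 99 × *s*:

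| *s* | Number missing it | Share of 300 |
|---|---|---|
| 25% | 24.75, about 25 | 8% |
| 50% | 49.5, about 50 | 17% |
| 75% | 74.25, about 74 | 25% |
| 100% | 99 | 33% |

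These count people absent from one visit. Some could attend a later follow-up, where adverse events are assessed again, so the number never formally assessed would be smaller by an unknown amount.

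**The case against.** The best defence is that the first 8 weeks are far from unmonitored. The eating-specific harm most relevant to a dietary trial is screened at weeks 2, 4 and 8, with a follow-up interview for high scores. Mood is assessed at week 4, and LIFE covers the interval between visits. A reader might infer from the schedule that events before week 8 are not systematically captured at all. The documents do not support that: these two domains are covered in both arms, and the week-8 assessment can pick up other events by recall.

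A reader might also infer that monthly review and reporting to the ethics committee within one week cannot be met for events first asked about at week 8. That does not follow either. The article does not say the week runs from onset. If it runs from when the team learns of the event, there is no conflict.

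Withdrawal is also better covered than the sentence on adverse events suggests. According to Intervention acceptability probes, the survey asks whether mood, sleep or quality of life worsened and puts open questions about problems. People withdrawn by the executive committee because of an event are, moreover, already known to the team.

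Finally, this is a condensed article, and it refers to a detailed manual with probes and decision rules that is not shown.

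Most of this stands and narrows the point. It does not remove it. The survey is requested, may not be completed, and is not described as an adverse-event assessment. The article also names the time points for formal assessment, and week 4 is not one of them. This is a schedule as stated, not a detail left to another document.

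**Conclusion.** The point holds in a limited form. Adverse events outside mood and eating-disorder symptoms are not formally asked about until week 8, and no formal query is stated for people who leave before then. The review by condition may therefore under-count events in early leavers. The documents do not show that it does so, or that any under-count differs by arm.

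The size is unknown. The range of about 25 to 99 of 300 rests on the planned 33% attrition and on an assumed 25% to 100% of it falling before week 8. It is an upper bound on people with no formal assessment at any time, for each assumed share, because later follow-ups could recover some.

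This is an inexpensive improvement to harms ascertainment. It does not bear on the validity of the primary comparison.

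**What to change.** 1. Add the adverse-event form used at post-intervention to the week-4 self-report battery, in both arms.
2. Use the same form at the withdrawal contact, alongside the acceptability survey and the call about reasons. A week-4 form cannot reach people who leave before week 4, so both additions are needed.
3. Collect it by self-report or through unmasked staff, so that masked interviewers do not hear details that reveal the assigned plan.
4. Reconcile the sections Adverse events, Reasons for discontinuation from study and Statistical analysis of the primary outcome, so that they agree on who is asked for a final assessment and whether it includes adverse events.

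The cost is one existing form at two existing contacts, a few minutes per participant. People who drop out of contact altogether before week 4 would still be missed.
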